## Abstract

**Trial registration:**

ClinicalTrials.gov Identifier: NCT06683105. Registered on 8 November 2024.

## Introduction

Inflammatory bowel disease (IBD) comprising of Crohn’s disease and ulcerative colitis, is characterized by chronic inflammation of the gastrointestinal tract due to an abnormal immune response to gut microbiota in genetically susceptible individuals [1]. Canada has among the highest burden of IBD in the world with a forecasted prevalence reaching 1.1% (470,000) by 2035 [2].

Food and nutrition have a profound impact on the lives of people living with IBD due to the impact of eating on symptoms, the psychosocial impact of food avoidance, the high prevalence of nutrition‐related problems and the role of nutrition in the management of disease [3–5]. One study demonstrated that the majority of participants (85.4%) believed that diet could trigger IBD relapses [6]. According to Bergeron et al. 2018, food exclusion rates are 69% higher in people experiencing a flare versus those in remission [7]. Food avoidance and restrictive diet patterns have been correlated with higher risk of malnutrition and poorer food related quality of life [8–10]. The intestinal involvement and inflammation further contribute to the high prevalence of malnutrition ranging between 20 and 85% in IBD patients with protein energy malnutrition and weight loss being the most common during active disease [11–13].

Nutritional therapies in IBD include therapeutic diet strategies to induce remission of active IBD and general recommendations to improve overall health and well-being [14]. Prospective cross-sectional cohort studies have linked the consumption of ultra-processed foods to the onset of IBD and among patients with diagnosis of IBD, a higher risk of IBD-related surgeries [15–17]. The evidence for induction of remission is strongest for exclusive enteral nutrition (EEN), particularly in the pediatric population, and the Crohn’s disease exclusion diet (CDED) [18,19]. However, these dietary treatments are challenging to follow and require guidance of a dietitian. There is emerging evidence to support anti-inflammatory diets such as Mediterranean Diet and Specific Carbohydrate Diet in treating active IBD. A prospective study of 142 people with IBD initiated on a Mediterranean diet demonstrated improvement in disease activity and quality of life [20]. A randomized trial comparing a specific carbohydrate diet to a Mediterranean diet in Crohn’s disease demonstrated no difference between the two diets in terms of symptomatic remission (~45%) and fecal calprotectin (~30–35%) response [21]. Additionally, researchers suggest that, based on its relative ease of following and additional health benefits, the Mediterranean diet may be a more practical option than the specific carbohydrate diet for most patients with mild to moderate Crohn’s disease [21]. Moreover, almost 50% of the participants experienced a clinical remission by 6 weeks of following the diets. Given that many dietary interventions have shown significant positive outcomes, including reduced gastrointestinal symptoms, reduced inflammation and improved quality of life, within 6–12 weeks of dietary intervention [21–25], a period of 8 weeks can be considered ideal to test in a pilot.

The recent American Association of Gastroenterology (AGA) 2024 guidelines provide specific recommendations for all IBD patients without contraindications to follow a Mediterranean eating pattern low in ultra processed foods [14]. Implementing these recommendations into practice can be challenging in settings without access to a dietician. Although gastroenterologists (GIs) may be aware and able to advise patients on the type of diet, few would have the expertise or time to provide specific details of the foods that are allowed or excluded in these diets. Published literature suggests significant gaps in knowledge relating to nutrition in IBD exist among health care providers. A survey of 223 providers demonstrated that only 51% of GIs rated their knowledge of nutrition in IBD as “very good” and 33% reported they did not routinely screen for malnutrition [26].

While apps for managing diet and lifestyle in IBD are becoming more common, few effectively support self-management or formally assess effectiveness in changing behavior or health outcomes. A recent review of available mobile health apps for IBD found that many IBD apps were designed for virtual care led by healthcare providers [27]. The study evaluated apps based on features like dietary support, goal setting, and behavior-change facilitation, highlighting apps such as LyfeMD [28], My IBD Care: Crohn’s and Colitis [29], MyGut App [30], Colitis Diary [31] and Crohn’s Diary [32]. Some apps were purely for tracking without educational information, and their effectiveness in improving behaviors, disease outcomes, or quality of life remains unclear. It was also unclear if there was patient engagement or input in the development of these apps. Although validated rating scales such as MARS (Mobile Application Rating Scale) [33] are often used to evaluate the quality of an app including engagement, functionality, aesthetic and information, it is not clear that these factors contribute to meaningful clinical outcomes. Therefore, we developed a nutrition guidance app (MyIBDDiet), co-designed with insights from patient research partners, to support patients living with IBD to self-manage and adopt a Mediterranean diet eating pattern.

## Objectives

This pilot study is designed to explore a structured approach to the evaluation of a mobile health app to empower self-management for people living with IBD. The primary study objectives are to evaluate the usability and acceptability of the MyIBDDiet app. The secondary objectives include evaluating the efficacy of the app in improving diet quality, diet knowledge, disease control, safety and quality of life.

## Materials and methods

### App development and device feasibility

We have co-developed a diet guidance and tracking app (MyIBDDiet) with patient research partners with the aim to improve diet quality and reduce inflammation. Features of the app allow for tracking of food intake using the Canadian Nutrient File (CNF) [34], and foods from the USDA (United States Department of Agriculture’s Food Data Central database) [35], CINE arctic nutrient file (Centre for Indigenous People’s Nutrition and Environment database) [36], INDB (Indian Nutrient Databank) [37], and OFF (Open Food Facts) [38] databases. It also tracks symptoms allowing users to correlate food intake with symptoms. The app provides immediate messaging feedback on the level of food processing [using NOVA classification [39]] and alignment of the participant’s food intake to an anti-inflammatory mediterranean-style eating pattern. A barcode scanner based on API food database helps users to identify foods with additives or emulsifiers that have been linked to IBD. Additionally, electronic resources and videos provide education on an anti-inflammatory pattern of eating, fiber and the intestinal microbiome, food additives and emulsifiers and practical substitutions in a restaurant.

As part of the app development process, device feasibility testing was conducted on version 1 of the app by academic researchers and patient research partners. Feedback primarily related to content clarity and interpretation as well as missing food categories and items, which led to incorporation of the Canadian Nutrition file database with more than 5000 foods along with additional foods from the USDA, CINE, INDB, and OFF databases expanding the available food choices to include branded foods and culturally appropriate foods. We aim to further expand the database based on the reporting of missing foods so that the database is oriented to include all the foods consumed commonly in the multi-cultural North American region. Moreover, clearer presentation and placement of information on food tags such as food processing level and mediterranean style eating pattern in the app were highlighted as areas for improvement. Foods were subsequently tagged into appropriate processing categories and Mediterranean-like eating tags by an experienced IBD dietitian. Additional feedback focused on interface layout and technical issues, including difficulties with video loading, symptom logging and app login functionality. These issues were resolved in a timely manner which provided us with an improved version 2 (V2) of the app suitable for use in the present study.

### Trial design and setting

This protocol was developed in accordance with the SPIRIT 2013 statement (S1 File). Fig 1 shows the SPIRIT schedule of enrollment, interventions and assessments. This single-centre, open-label pilot randomized trial will be conducted at the University of Alberta hospital, a tertiary care hospital located in Edmonton, Alberta. Participants will be randomized in a 1:1 ratio to either the Intervention Arm (receiving MyIBDDiet app for the entire duration of the study, i.e., 60 days) or the Control Crossover Arm (receiving usual care as per treating physician for the first 30 days followed by MyIBDDiet App for the latter half of the study) (Fig 2). Outcomes of interest will be assessed at baseline, 1 month, 2 months, and at 6 months follow-up. The 6-month timepoint will allow for assessment of persistence of behavioral and diet quality changes.

**Fig 1 pone.0353123.g001:**
[figure not shown]
SPIRIT schedule of enrollment, interventions, and assessments. PRO-2 UC = Patient-Reported Outcome for ulcerative colitis, PRO-3 CD = Patient-Reported Outcome for Crohn’s disease, Mini-EAT = Mini-Eating Assessment Tool, EQ-5D = EuroQol, SIBDQ = Short Inflammatory Bowel Disease Questionnaire, MAUQ = mHealth App Usability Questionnaire, TFA = Theoretical Framework of Acceptibility, ASA24^®^ = Automated Self-Administered 24-Hour Dietary Assessment Tool, CRP = C-reactive protein, FCP = fecal calprotectin.

**Fig 2 pone.0353123.g002:**
[figure not shown]
Overview of the Study Design.

### Sample size

We aim to recruit 40 people living with IBD (20 in each arm). As this is a pilot feasibility and usability study, a formal power calculation was not done. The sample size of n = 40 (n = 20 each arm) is based on established recommendations for pilot trials, where it has been suggested that a minimum of 12–30 participants per arm are sufficient to estimate the variance required for a future power calculation [40,41]. The results of this pilot study will inform the sample size calculation for a future larger, multi-centre randomized trial to evaluate efficacy of MyIBDDiet App. Participants will be recruited for semi-structured interviews until thematic saturation is reached.

### Risk mitigation plan

The IBD Clinic at the University of Albertan actively follows approximately 5100 patients with IBD across a team of seven dedicated IBD physicians, representing a substantial and stable patient population to support recruitment for this trial. To further mitigate the risk of slower than anticipated recruitment, we will implement supplementary recruitment strategies, including distributing ethics approved recruitment materials through ethics approved social media platforms and University of Alberta newsletters. This has been a successful recruitment strategy for our previous studies.

### Eligibility criteria

The inclusion and exclusion criteria are outlined as below.

**Inclusion Criteria:**

Age ≥ 18 yearsAble to provide informed consentEstablished diagnosis of IBD determined by treating physicianNot in acute flare (inability to tolerate fibre diet)Willing and able to adhere with all required study proceduresAble to read and speak English

**Exclusion Criteria:**

Short bowel syndromeHigh ostomy outputIntestinal stricturesPregnancy or breastfeedingMalnutrition [screened by Canadian Nutrition Screening Tool (CNST)]Not willing or able to comply with all required study proceduresConditions requiring dietary restrictions (e.g., celiac disease, kidney disease, diabetes, eosinophilic esophagitisHave other conditions that may require low fibre diet such as irritable bowel syndrome, gastroparesisCurrently on a therapeutic diet for IBD or using diet tool for IBD (e.g., Nutrition or diet Apps, specific carbohydrate diet, EEN, CDED, Mediterranean or anti-inflammatory diet)Active malignancy

### Criteria for discontinuation

Participants can withdraw from the trial at any time at participant’s request, if there are adverse effects or worsening of IBD

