### Statistical analysis plan

The main analytical steps in this study include descriptive statistics, pre-post comparisons, and between-group comparison tests. All quantitative analyses will be conducted on an intention-to-treat (ITT) basis, including all participants who undergo randomization [55]. This pilot randomized study will be conducted over 60 days, comprising two 30-day periods of app use.

Primary and secondary quantitative outcomes: To account for the repeated measures (Baseline, Day 30, Day 60, Day 180) and the crossover study design, we will utilize Linear Mixed Models (LMM) [56,57]. This approach is preferred as it handles missing data robustly via Restricted Maximum Likelihood (REML) estimation and accounts for within- subject and between-subject variability. The model will include “Group”, “Time” and “Group X Time” interactions as fixed effects, with a random intercept for each participant. In the event of model non-convergence, the random effects structure will be simplified.

Handling of missing data: We anticipate an attrition rate of 10–15%. Linear Mixed Models allow for the inclusion of participants with missing timepoints under missing at random assumption. If missing data exceeds 20%, Multiple imputations by chained Equations (MICE) will be performed [58].

Effect size and Variance: As this is a pilot study, the focus of analysis is not solely on p-values, but on point estimates and confidence intervals. We will calculate Cohen’s d effect sizes for change in quantitative outcomes to provide the necessary variance and magnitude of effect estimates required for a power calculation in a future larger trial. We will be using SPSS version 29.0.2.0 (20) for statistical analyses.

Semi-structured interviews: The interviews will be transcribed verbatim. Thematic analysis will be done independently by two researchers using Nvivo which is a qualitative data analysis software and any conflicts will be resolved by a third reviewer who is a senior gastroenterologist and principal investigator [59].

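### Withdrawal for worsening IBD makes missing at random doubtful for disease activity and quality of life, and the MICE fallback above 20% missing neither reveals nor corrects this

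*Protocol article*

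**What the plan says.** Under Criteria for discontinuation, the protocol article allows withdrawal from the trial at any time at the participant's request, and names as circumstances "if there are adverse effects or worsening of IBD". The section does not say whether outcomes are still collected afterwards.

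The Statistical analysis plan section applies a REML linear mixed model to the quantitative outcomes over baseline and Days 30, 60 and 180: "The model will include “Group”, “Time” and “Group X Time” interactions as fixed effects, with a random intercept for each participant". Analysis is by intention to treat, "including all participants who undergo randomization". On missing data it says "Linear Mixed Models allow for the inclusion of participants with missing timepoints under missing at random assumption", expects attrition of 10–15%, and adds one contingency: "If missing data exceeds 20%, Multiple imputations by chained Equations (MICE) will be performed". It names no imputation variables.

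The outcomes section lists PRO2/PRO3, CRP, fecal calprotectin, EQ-5D and SIBDQ as secondary. It also provides for adverse event monitoring at visits, and between visits if symptoms worsen. The estimates have a further use: Cohen's d for change and its variance are to feed the power calculation of a larger trial.

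**The concern.** Missing at random requires that, given the scores already observed, the chance of dropping out does not depend on the unseen score. A rule that links leaving to worsening puts this in doubt for outcomes that measure worsening. The eligibility criteria admit only people who are not in acute flare. Someone who worsens and leaves before Day 30 therefore contributes one score from a non-flare state, and that score cannot carry the worsening.

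The fallback responds to how much is missing, not to why. Standard MICE built on the same visit scores borrows from participants who stayed and looked similar beforehand, as the mixed model does. Agreement between the two would therefore reassure without having tested the assumption at risk.

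What is at stake is the pre-post change within each arm, and the effect sizes and variances carried forward. The primary outcome, usability, is not the subject of this point.

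**Working it through.** **No figure of the plan to reproduce.** The sample size section says "a formal power calculation was not done". The 40 participants are 2 × 20, and 20 per arm lies within the cited 12–30.

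**Would the fallback run?** Reading the 20% as a share of participants:
- 10% attrition: 40 × 0.90 = 36 remain (18 per arm).
- 15% attrition: 40 × 0.85 = 34 remain (17 per arm).
- Trigger: more than 40 × 0.20 = 8 lost. The forecast is 4 to 6 lost, so on the plan's own expectation MICE is not used.

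**Bias under dropout that follows unseen worsening.** Inputs from the protocol: four visits, the planned random-intercept model and 10–15% attrition. Assumptions: outcome SD 1 with higher better, true change 0 in both arms, within-person correlation 0.5 or 0.7, and dropout at Day 30 or Day 60 with a logistic slope of 2 per SD of unseen worsening. Simulation used 8,000 per arm to isolate bias (noise about 0.03 or less). Single stochastic sequential-regression imputation on the same scores stood in for MICE.

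| Dropout | Mixed-model bias (SD) |
|---|---|
| 15%, depends on last observed score (missing at random) | within-arm change −0.03 to 0.00 |
| 10%, unseen worsening, both arms | within-arm change to Day 60 +0.05 to +0.06 |
| 15%, unseen worsening, both arms | within-arm change to Day 60 +0.09 to +0.12 |
| 25%, unseen worsening, both arms | within-arm change to Day 60 +0.14 to +0.18 |
| Equal unseen-worsening dropout in both arms | between-arm difference within 0.02 of zero |
| 25% app, 5% control, unseen worsening | between-arm difference +0.08 to +0.13 |
| 5% app, 25% control, unseen worsening | between-arm difference −0.06 to −0.16 |

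Imputation agreed with the mixed model to within about 0.02 SD in every scenario.

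**Upper bound.** Take one baseline and one follow-up score, bivariate normal, and remove exactly those with the worst change. The follow-up mean is then estimated by regression under missing at random:
- 10% removed: bias 0.16 SD (correlation 0.5) or 0.13 SD (0.7).
- 15% removed: bias 0.23 SD (0.5) or 0.19 SD (0.7).
- 15% lost, half of them the worst and half at random: 0.12 SD (0.5) or 0.10 SD (0.7).

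Regression imputation gave the same values to within 0.001 SD.

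**Variance passed on.** In the same two-score setting, the SD of change among those who stay shrinks as follows:
- Half selection: to 0.90 of its true value at 10% loss and 0.87 at 15%.
- Full selection: to 0.84 at 10% loss and 0.80 at 15%.

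Sample size scales with SD². The half case alone would therefore understate a future N by 1 − 0.90² = 19% to 1 − 0.87² = 24%. Equal dropout in both arms does not cancel this.

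**Scale.** The standard error of a between-arm difference in change with 20 per arm is √(2(1 − ρ) × 2/20), which is 0.32 SD at ρ = 0.5 and 0.24 SD at ρ = 0.7.

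**The case against.** The strongest reply is that this is a condensed article. Follow-up after withdrawal, recorded reasons and sensitivity analyses usually sit in the full protocol or analysis plan, and a mixed model under missing at random is a standard main analysis. That stands as far as it goes: no fault lies in those details being unwritten, or in the choice of model. It does not cover the contingency that the article does fix, with its threshold and method. That contingency cannot address the loss that the article's own withdrawal wording invites.

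Other parts of the reply stand and limit the point:
- Withdrawal for worsening is compatible with missing at random when earlier scores already show the decline. The simulated bias is then essentially nil.
- A reader might infer that worsening between visits goes unmeasured. The outcomes section provides for adverse event monitoring in that interval, and those records could inform an imputation. The article does not say that they will.
- App use is self-directed with no minimum, so a participant can already stop using it and stay in the trial.
- A reader might infer that intention to treat is breached. It is not: missing values do not void it, and the mixed model keeps randomised participants with any observed score in their assigned arm.
- The affected outcomes are secondary, 4 to 6 people are expected to leave, and the bias is smaller than the standard error of the between-arm difference.

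**Conclusion.** The point holds as a risk. Missing at random is doubtful for disease activity and quality of life, and the stated fallback shares the assumption when it uses the same scores and is not expected to run.

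If dropout of 10–15% follows unseen worsening, within-arm change may look better than it is by roughly 0.05–0.12 SD. The 0.13–0.23 SD figure is an upper bound that needs every leaver to be among the worst. The variance for the next trial may be understated as well. These sizes rest on assumed correlations of 0.5–0.7 and an assumed strength of selection; the protocol gives neither.

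It is tempting to read this as showing that the results will favour the app. The documents do not support that. The favourable direction applies to within-arm change only. The randomised contrast is close to unbiased if such dropout is equal, and shifts for or against the app if it is not. Nothing in the protocol says which arm would lose more people.

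**What to change.** **Criteria for discontinuation.** Distinguish stopping the app from withdrawing from data collection. When a participant stops, record the reason and PRO2/PRO3. Continue the Day 30, 60 and 180 questionnaires unless consent for data collection is withdrawn. This leaves unchanged when a participant may stop.

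**Statistical analysis plan.** Keep the mixed model as the main analysis at any rate of missing data. Replace the 20% MICE trigger with a delta-adjusted sensitivity analysis. In it, participants who leave for worsening or adverse effects are given progressively worse imputed values, with recorded adverse events and withdrawal reasons as auxiliary data.

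**Cost.** Protocol and analysis wording, a few extra remote questionnaires and one more sensitivity analysis. The wording on data at exit should be settled before recruitment, since exit data not recorded at the time cannot be recovered later. This is a cheap improvement.

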### Enrollment and randomization

Potential participants, who may have been referred to this study through their primary care physician/gastroenterologist or self-referred by responding to recruitment posters, will be given a copy of the informed consent form (ICF) for review at their convenience. At a scheduled call or in-person visit, a member of the study team will explain the study in detail, answer any potential questions and obtain written informed consent from those who agree to take part in the study. Once informed consent is received, eligibility will be confirmed by accessing the medical charts for determining alignment with the eligibility criteria. Eligible participants will be enrolled in the study, scheduled for their baseline visit and randomized in a 1:1 ratio to either of the two study arms: Early Intervention Arm and Delayed Intervention Arm. Randomization will be performed using Research Electronic Data Capture (REDCap) [42] software hosted at the University of Alberta.

